#### **7.9. Single Dose Escalation Visits**

At each visit, participants will return to the Imperial CRF to receive treatment with nicotinamide. They will be admitted to the Imperial CRF and the following assessments will be performed:

- Vital signs assessment (pulse rate, blood pressure, respiration rate, pulse oximetry and temperature), these will be repeated prior to each blood sample being taken (see below).
- Assessment and recording of AEs since baseline throughout the visit
- Review of concomitant medications
- If participants experience nausea they will be given a VAS to rate the severity.
- Each participant will be given an oral dose of nicotinamide (as detailed in schema).
- Blood samples taken for standard clinical laboratory tests (haematology, chemistry, and LFTs), blood glucose will be measured using a BM stick at predose and 24 hours following nicotinamide administration.
- Blood samples to assess FXN level will be taken predose and at 2 ( $\pm$  15 mins), 4 ( $\pm$  25mins), 8 ( $\pm$  1) and 24 ( $\pm$  2.5) hours following nicotinamide administration.
- On the last dosing visit blood samples for the separate Chromatin immunoprecipitation studies will be taken at pre-dose and at 8 ( $\pm$  1) hours post-dosing.
- Participants will spend the day within the Imperial CRF and return home after the last blood test. They will return the following day for the 24 hour blood test. In some cases, if travel is difficult, participants may be offered overnight accommodation either at the Imperial CRF or private accommodation.
- All participants will be reviewed by the CI or delegates prior to discharge.

#### **7.10. Multiple dose study**

##### **Part II**

The multiple dose study is similar to the single dose study and will commence after a washout interval of at least one week.

- Participants will be admitted for four nights within the Imperial CRF and return home after the last blood test on day 5. It may be possible in certain exceptional circumstances for some participants to return home every evening. This would need to be agreed by the CI.

- The ratio of participants that will be 'on no nicotinamide' to those on 'on nicotinamide' will be 1:4 (i.e one patient will be on 'no treatment' to 4 'on treatment'). Participant's allocation to no drug will be determined at the CI's discretion and discussed with the participant. The daily dosing regimen may be modified at the CI's discretion. The daily dosing regimen may be modified from once to twice a day for some participants at the CI's discretion.
- Vital signs assessment (pulse rate, BP, respiration rate, pulse oximetry and temperature) will be repeated prior to each blood sample being taken.
- ECG will be taken predose on day 1 and prior to discharge on day 5.
- Assessment and recording of AEs from baseline throughout the visit
- Review of concomitant medications
- In order to avoid nausea, participants will be administered anti-nausea treatment if required (domperidone, 20 mg oral, metoclopramide etc) prophylactically pre-dose and post-dose (domperidone, 20 mg oral up to four times daily; metoclopramide 10-20 mg IV PRN up to three times daily etc).
- If participants experience nausea they will be given a VAS to rate the severity.
- Blood samples for clinical chemistry, haematology will be taken daily immediately prior to dosing.
- Blood samples to assess FXN level will be taken daily pre-dose and at 2 ( $\pm$  15 mins), 4 ( $\pm$  25mins), 8 ( $\pm$  1) hrs following nicotinamide administration. The pre-dose sample will also represent the 24 hour sample of the previous day. The last 24 hour sample will be taken on day 4. On the last day, the last 8hr PK sample may be taken ( $\pm$ 2)hrs as the Imperial CRF closes at 6pm on Fridays.
- Further blood samples for the chromatin immunoprecipitation will be taken at pre-dose on day 1 and day 5.
- Participants and their carers will complete Part II of FARS. Neurological assessment (SARA and SCAFI scales) and a clinician- and/or software-based speech dysarthria assessment will also be performed on day 1 and day 5.
- All participants will be reviewed by the CI or delegates prior to discharge.
- Prior to discharge participants will be provided with the study drug supply and rescue medication (typically domperidone or metoclopramide) to take if required prophylactically pre-dose (domperidone, 20 mg oral) and post-dose (domperidone, 20 mg oral) up to four times daily when necessary until the day of the first visit of Part III is scheduled (if applicable).

### Part III

If the multiple dose dosing regimen of nicotinamide in Part II is well tolerated and changes in FXN level are observed, all participants (including those who were scheduled to receive no drug in part II) will be offered to enter Part III. Participants who participated in part I but not in part II of the study will be allowed to participate. These participants may require re-screening. This decision will be taken by the CI. If required, additional participants will undergo screening and if eligible may enter directly into this part of the study.

Participants who were 'on drug' in Part II will take their MTD already established over the course of two months. If any AEs occur that in the CI's opinion may put the safety of the participant at risk, the dose schedule will be adjusted. If a participant was on 'no drug' in Part II or due to enter Part III directly they will start at a low dose of nicotinamide (typically 2g) which will be gradually escalated in the absence of any AEs which in the CI's opinion may put the participant's safety at risk.

Participants who took part in Part II will be given the weekly drug supply and diary on Part II Day 5. Participants who took part in Part I but not Part II or participants who will directly enter Part III will be given the weekly drug supply and diary at their screening visit (only once determined eligible) or by courier / recorded delivery post. Their next visit will be Part III, week 1.

If the participant stops taking nicotinamide for several days (for safety reasons), only once the participants AEs are fully resolved. The CI may decide to add this drug interruption period onto the end of the two month period.

To ensure that sustained FXN upregulation is achieved, the nicotinamide PK/PD relationship [i.e. time to nicotinamide steady state vs. upregulation of FXN] will be evaluated at each weekly visit and the daily dose regimen may be modified from once to twice a day [i.e. from 6 grams (or MTD) OD to 3 grams (or ½ MTD) BD]. Participants will come to the Imperial CRF prior to taking their dose of nicotinamide once a week ( $\pm 2$  days) over this time period.

In order to ensure compliance, participants will be instructed to complete a weekly trial diary for the entire duration of Part III until the end-of-study visit. The first weekly trial diary will be given to the participant prior to discharge on day 5 of Part II or at screening or recorded delivery post or courier if participants are participating in Part III only. Participants will record any AEs and concomitant medications from the next day until their next visit.

Each week, the trial diary from the previous visit will be collected and participants will be provided with another diary to complete starting on the next day. Participants will be provided with anti-nausea treatment as rescue medication; they will be asked to keep an accurate record of use in the trial diary.

At each visit:

- Participants will come to the Imperial CRF and return home after dosing.
- Vital signs assessment (pulse rate, BP, respiration rate, pulse oximetry and temperature), these will be taken predose.
- ECG will be taken predose and if necessary before discharge (in cases where the participant will be staying for 8hrs post-dose).
- Assessment and recording of AEs since baseline throughout the visit
- Review of concomitant medications
- Blood samples taken for standard clinical laboratory tests (haematology, chemistry, and LFTs), blood glucose will be measured using a BM stick at predose.
- Blood samples to assess FXN level will be taken predose and if necessary at 8hrs post-dose.
- Participants will be given a trial diary.
- All participants will be reviewed by the CI or delegate prior to discharge. Participants will be provided with the study drug supply and rescue medication (if required) until the day of their next scheduled visit. Rescue medication (anti-nausea treatment, typically domperidone or metoclopramide) should be taken if required prophylactically pre-dose (domperidone, 20 mg oral) and post-dose (domperidone, 20 mg oral up to four times daily when necessary).

The following assessment will be performed on bi-monthly visits (visits 2, 4, 6 and 8):

- Participants and their carers will complete Part II of FARS bi-monthly. Neurological assessment (SARA and SCAFI scales) and a clinician- and/or software-based speech dysarthria assessment will also be performed.

The following assessment will be performed on monthly visits (visits 4 and 8):

- Blood samples for the separate chromatin immunoprecipitation studies will be taken predose.

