### **Long term assessment of FRDA participants taking nicotinamide daily over a two month period, Part III**

If the multiple dose dosing regimen of nicotinamide in Part II is well tolerated and changes in FXN level are observed, all participants (including those who were scheduled to receive no drug in part II) will be offered to enter Part III. Participants who took part in part I but not in part II of the study may also participate. These participants may require re-screening. This decision will be taken by the CI. If required, additional participants will undergo screening and if eligible may enter directly into this part of the study. Participants who took part in Part II will be given the weekly drug supply and diary on Part II Day 5. Participants who took part in Part I but not Part II or participants who will directly enter Part III will be given the weekly drug supply and diary at their screening visit (only once determined eligible) or by courier / recorded delivery post. Their next visit will be Part III, week 1.

Participants who were 'on drug' in Part II will take their MTD already established over the course of two months. If any AEs occur that in the CI's opinion may put the safety of the participant at risk, the dose schedule will be adjusted. If a participant was on 'no drug' in Part II or due to enter Part III directly they will start at a low dose of nicotinamide (typically 2g) which will be gradually escalated in the absence of any AEs which in the CI's opinion may put the participant's safety at risk.

If the participant stops taking nicotinamide for several days (for safety reasons), only once the participants AEs are fully resolved, the CI may decide to add this drug interruption period onto the end of the two month period.

To ensure that sustained FXN upregulation is achieved, the nicotinamide PK/ pharmacodynamic (PD) relationship (i.e. time to nicotinamide steady state vs. upregulation of FXN) will be evaluated at each weekly visit and the daily dose regimen may be modified from once to twice a day [i.e. from 6 grams (or MTD) Once Daily (OD) to 3 grams (or ½ MTD) twice a day (BD)]. In some instances, manufacturing restrictions (i.e. nicotinamide tablets of 500mg) render the division of the dose into two equal doses, for BD dosing, impossible. In these cases patients will receive a slightly different dose in the morning to the evening.

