Participants will attend the Imperial CRF prior to taking their dose of nicotinamide once a week ( $7 \pm 2$  days) over this time period. Participants will be provided with study drug supply for  $7 \pm 2$  days and rescue medication (anti-nausea treatment, typically domperidone or metoclopramide). Domperidone or metoclopramide will be taken if required prophylactically [domperidone pre-dose (20 mg oral) and post-dose (20 mg orally up to four times daily)]. Participants will also be provided with their first weekly diary card, which will need to be completed each day for the entire duration of Part III until the interventional end-of-study visit. Participants will record whether or not they took nicotinamide, number of tablets, any AEs and any concomitant medications taken. Each week, the trial diary from the previous visit will be collected and participants will be provided with another diary to complete starting on the next day. Participants and their carers will complete Part II of the Friedreich's Ataxia Rating Scale (FARS): ADL. SARA and SCAFI scales will also be done and a clinician- and/or software-based speech dysarthria assessment will be performed.

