#### 5.5. Study Product

A highly purified form of nicotinamide which has been shown to be well tolerated orally and is readily available for therapeutic use will be used for this study. The preparation of nicotinamide has been sourced by the Hammersmith Hospital Pharmacy who will dispense the drug. The IMP may be dispensed up to 2 days prior to the participant's visit. In Part I, the IMP will be dispensed at each visit. In part II, the IMP will be dispensed for the whole week. In Part III, the IMP will be dispensed at each weekly visit.

Participants will be given the drug supply required either on PIID5 (for participants participating in Part II) or at the screening visit / recorded delivery post (for participants who participated in part I but not in part II / participants who will directly enter into Part III) until their next visit (Part III, week 1).

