#### **7.11. End of Interventional Study Follow-up Visit**

After at least a 1 week and at most 8 weeks washout interval for the interventional study participants will return to the Imperial CRF for routine medical assessment and the following safety assessments will be performed:

- Review concomitant medications
- AE assessment

- Physical examination including vital signs (pulse rate, BP, respiration rate, pulse oximetry and temperature) and assessment of level of disability, using FARS, SARA, SCAFI and speech dysarthria assessment.
- 12-lead ECG in the supine position
- Blood and urine samples will be taken for clinical laboratory assessment (haematology, clinical chemistry, electrolytes, coagulation, fasting lipid profile, enzymes and urinalysis). Blood glucose will be measured using a BM stick. A blood sample for FXN level will also be taken.
- A blood sample for the separate chromatin immunoprecipitation study will be taken.

Participants will be discharged from the interventional study when considered appropriate by the CI.

We do not recommend that participants continue to take nicotinamide post-study as further clinical trials are required to determine whether or not nicotinamide is safe and is of clinical benefit to patients with FRDA. If participants still decide to take nicotinamide against our advice, they will be referred to their GP with recommendation of regular safety follow up to evaluate any nicotinamide-induced toxicity. We may request the FRDA participants consent to come in for visits at the Imperial CRF at the CI's discretion. Blood tests (FXN/chromatin, safety bloods etc) and neurological and medical examinations (SARA, SCAFI, ADL, ECG, vital signs etc) may be performed at these visits.

If the interventional project is successful, FRDA participants may be approached for future research in the same area. It will be entirely up to the participant to decide whether to consent to participation in any future interventional research study.

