| FARS, SARA, SCAFI and speech dysarthria assessment                                    |                                   | X                                | X                                                |
| Chromatin studies                                                                     |                                   | X*                               | X                                                |
| FXN measurement pre-dose and 8hrs post-dose if necessary                              | X                                 | X                                | X                                                |
| Nicotinamide and anti-nausea tablets                                      | X                                 | X                                |                                                  |
| Trial diary                                                                           | X                                 | X                                |                                                  |

\* Pre-dose chromatin samples to be taken monthly (at weeks 4 and 8).

\*\* NB Participants who elect to only participate in either the single dose study (part I) or part II of the multiple dose but not both will have the final visit between 1 and 8 weeks after visit 5 of either the single dose or day 5 of the multiple dose part of the study.

If the participant elects to take part in all parts of the interventional study (Parts I, II and III) or only in Part II and Part III, participants will have the final visit between 1 and 8 weeks after day 5 of the multiple dose Part II of the study or visit 8 of the multiple dose Part III.

1. Urinalysis include: appearance, color, pH, specific gravity, ketones, protein, glucose, bilirubin, nitrite, urobilinogen
2. Haematology include: white blood cell count with differential, red blood cell count, platelet count, hemoglobin, and hematocrit
3. Chemistry include: albumin, total bilirubin, urate, total cholesterol, creatinine, low-density and high-density lipoproteins, total protein, triglycerides, uric acid, Aspartate aminotransferase/glutamate oxalo-acetate transaminase (AST/GOT); alanine aminotransferase/glutamate pyruvate transaminase (ALT/GPT);  $\gamma$ -glutamyl transpeptidase (Gamma-GT); alkaline phosphatase (AP); lactate dehydrogenase (LDH); creatine kinase (CK)

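### Part III issues nicotinamide at visit 8, yet the time from visit 8 to the End of Study visit is declared a washout of at least 1 week

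*Protocol*

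**What the plan says.** Three places in the Protocol put drug in the participant's hands at visit 8.

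- Section 5.5: "In Part III, the IMP will be dispensed at each weekly visit".
- Section 7.10, Part III, in the list of actions for each visit: "Participants will be provided with the study drug supply and rescue medication (if required) until the day of their next scheduled visit". The same section names visit 8 among the Part III visits and does not except it.
- Section 12.1, Part III table: the row "Nicotinamide and anti-nausea tablets" is marked in the column for weeks 2, 4, 6 and 8, and is blank at End of Study.

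The first pack is issued earlier. Sections 4.1 and 7.10 have it given on Part II day 5, or at screening or by courier or post, before the week 1 visit. Section 4.1 sets the pack size at 7 ± 2 days, in the sentence that begins "Participants will be provided with study drug supply for", and the length of Part III at two months.

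After visit 8 the only interventional visit left is End of Study. Section 7.11 places it thus: "After at least a 1 week and at most 8 weeks washout interval for the interventional study". For those who go through Part III, section 12.1 counts the same interval from visit 8: "between 1 and 8 weeks after day 5 of the multiple dose Part II of the study or visit 8 of the multiple dose".

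Sections 4.1 and 7.10 also provide for a safety interruption. Once the adverse events have resolved, "the CI may decide to add this drug interruption period onto the end of the two month period".

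**The concern.** The same interval, visit 8 to End of Study, is treated as a period for which drug is supplied and as a period off drug. A site that follows sections 5.5 and 7.10 as written sends participants home from visit 8 with nicotinamide. A site that follows section 7.11 assumes they have none.

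Two things are at stake.

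- **Safety follow-up.** Section 8 names reversible abnormal liver function as a risk and relies on liver function tests throughout. The weekly chemistry and ECG end at visit 8. Section 7.6 budgets exactly eight weekly Part III chemistry samples and one at End of Study. Any dosing after visit 8 falls outside that weekly schedule.
- **Meaning of the End of Study values.** That visit collects chemistry, ECG, FXN, chromatin, FARS, SARA and SCAFI. If some participants are still on drug or just off it and others are weeks off it, the values do not share one treatment status. Reversal of a laboratory change, or persistence of an FXN change, is then hard to read from them.

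**Working it through.** The check is calendar arithmetic.

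**Inputs**
- Weekly Part III visits: 8, nominally 7 days apart (4.1, 7.10, 12.1).
- Packs: 1 before week 1 (4.1, 7.10), then 1 at each visit (5.5, 7.10).
- Pack size *s*: 5 to 9 days, nominal 7 (4.1).
- End of Study: *E* = 7 to 56 days after visit 8 (12.1).
- Required washout: at least 7 days (7.11).

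**The plan's own figures.** Visit 8 falls nominally on day 8 × 7 = 56. If nothing is issued at visit 8, dosing ends there and the washout equals *E*, that is 7 to 56 days. This reproduces the 1 to 8 weeks in both 7.11 and 12.1. Those two sections therefore fit together only if dosing stops at visit 8.

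**Pack count.** 1 + 8 = 9 packs, against 8 weekly intervals up to visit 8. The ninth pack is for use after visit 8.

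**With a pack at visit 8.** Assume that earlier packs are used up by visit 8 and that the last one is taken in full. Dosing days = 56 + *s*. Washout = *E* − *s*. The earliest End of Study visit with a 7-day washout is *E* = 7 + *s*.

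| Pack at visit 8 | Total dosing days | Washout, *E* = 7 | Washout, *E* = 56 | Earliest *E* that meets 7.11 |
|---|---|---|---|---|
| none | 56 | 7 | 56 | 7 |
| 5 days | 61 | 2 | 51 | 12 |
| 7 days | 63 | 0 | 49 | 14 |
| 9 days | 65 | −2 | 47 | 16 |

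A washout of −2 means that two days of drug remain at the End of Study visit. The conflict therefore sits at the early end of the window. Days 7 to 11 fail for every pack size, days 12 to 15 depend on the pack, and from day 16 both rules can be met.

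**Added interruption period.** Suppose dosing runs *k* days past visit 8 to make up missed days. The washout is then *E* − *k*. At *E* = 7 any *k* of 1 or more breaks the 1-week minimum, and *k* = 7 leaves none. The Protocol gives no figure for *k*; it speaks only of several days. This assumes that the weekly visits keep their dates during the interruption. The text does not say whether visit 8 moves.

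**Section 7.10 read alone.** If the visit 8 supply had to last to the next scheduled visit, then *s* = *E*: 7 to 56 extra days, 63 to 112 in total, and a washout of 0 throughout.

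**The case against.** A reader might infer from section 7.10 alone that participants could take up to 8 further weeks of drug, doubling the exposure. The Protocol does not support that. Section 4.1 sets the supply at 7 ± 2 days, sections 4.1 and 7.10 limit treatment to two months, and section 7.11 calls the interval a washout. Site staff would have to set all three aside. Nor is the period wholly unmonitored. Sections 4.1 and 7.10 keep the diary going until End of Study (section 4.1 has it record tablets and adverse events), and section 8.7.1 records adverse events to the end of follow-up. What is missing is a scheduled visit, bloods or ECG.

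Other points on that side have some weight:

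- **The rules can be met together.** With a 5 to 9 day pack this is true from day 16 after visit 8, and the minimum in 7.11 could be read as barring an earlier visit. But 12.1 allows day 7, counted from visit 8, and tells nobody to wait for the last pack to run out.
- **The week 8 mark is weak.** It sits in a grouped column and could stand for the visit-day dose. This is fair, but 5.5 and 7.10 carry the point without the table.
- **Two months need not mean 56 days.** If it means about 61 days (an assumption), a short last pack is near the planned duration. That bears on whether the days are extra. It does not restore the washout.
- **The interruption is discretionary and needs resolved events.** Section 7.10 follows it with weekly attendance over the period, which could cover the added days. The 12.1 table still shows no visit after week 8 except End of Study.
- **No objective in section 3 is an off-drug endpoint.** This stands. The loss is to the reading of follow-up data, not to the primary outcome.

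**Conclusion.** The inconsistency is real and lies in operative text. Following the dispensing rules as written, with the 7 ± 2 day pack, adds about 5 to 9 days of drug after visit 8 with diary cover only. If End of Study falls 7 days after visit 8, about 0 days of washout remain (range −2 to 2), against a stated minimum of 1 week. The shortfall is confined to End of Study visits before about day 16, or day 12 with the smallest pack.

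The figures assume nominal 7-day visit spacing, no tablets carried over from earlier packs, and a last pack taken in full. The interruption limb rests on the further assumption that visit 8 does not move when dosing is paused.

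**What to change.** Reconcile sections 4.1 (Part III), 5.5, 7.10 (Part III), 7.11 and the Part III table and notes in 12.1, so that they give one answer to each of three questions:

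1. Is nicotinamide issued at visit 8?
2. From which day are the washout and the End of Study window counted?
3. Which scheduled assessments, if any, cover a treatment period added after an interruption?

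Which answers are right is for the sponsor and the investigator to decide. The cost is a protocol wording change and one schedule column, plus whatever visits the sponsor chooses to schedule for participants whose treatment is extended.
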